## Abstract

**Background:**

Chronic low-back pain is a leading cause of global disability, with degenerative disc disease (DDD) recognized as a common structural contributor. While conservative therapies may provide temporary symptom relief, they do not address the underlying degeneration of the intervertebral disc. Surgical interventions, such as spinal fusion or total disc replacement, are invasive procedures that permanently alter the anatomical structure of the vertebral motion segment. Minimally invasive intradiscal therapies have the potential to bridge the treatment gap between non-surgical management and surgery. Intradiscal delivery of nucleus pulposus (NP) allograft is intended to structurally supplement the degenerating disc and restore native disc function. Preliminary studies have suggested that a single intradiscal administration of NP allograft (VIA Disc NP) may improve pain and function in patients with lumbar discogenic pain.

**Methods:**

This is a randomized, double-blind, sham-controlled, multi-center clinical trial designed to evaluate the safety and efficacy of VIA Disc NP. Eligible participants are 22 to 85 years of age with MRI-confirmed lumbar DDD (modified Pfirrmann grade 3–7), axial low-back pain of at least 6 months’ duration, and functional impairment unresponsive to conservative treatment. Participants are randomized in a 2:1 ratio to receive either a single injection of VIA Disc NP or a sham procedure. The primary efficacy endpoint of this superiority trial is the proportion of participants achieving a ≥ 30% reduction in back pain severity at 12 months. Secondary endpoints include functional improvement (ODI), quality-of-life measures (EQ-5D-5L, PGIC), and opioid reduction. Sham participants who remain symptomatic at 12 months may cross over to receive active treatment.

**Discussion:**

This trial will provide level-1 evidence of the safety and efficacy of supplemental NP allograft therapy in patients with moderate to severe lumbar discogenic pain. If successful, this approach may offer a minimally invasive, durable, and structure-preserving treatment alternative to spinal fusion or disc arthroplasty in a population with limited therapeutic options.

**Trial registration:**

This trial is prospectively registered at ClinicalTrials.gov (Identifier: NCT06778447). Registered on January 16, 2025

**Supplementary Information:**

The online version contains supplementary material available at 10.1186/s13063-026-09826-w.

## Administrative information

Note: the numbers in curly brackets in this protocol refer to SPIRIT checklist item numbers. The order of the items has been modified to group similar items (see http://www.equator-network.org/reporting-guidelines/spirit-2013-statement-defining-standard-protocol-items-for-clinical-trials/).

## Introduction

### Background and rationale {6a}

Lumbar discogenic pain associated with degenerative disc disease (DDD) contributes to substantial functional impairment and disability and has been identified as an important clinical target for therapeutic intervention [1, 2]. Degenerative changes within the nucleus pulposus (NP) contribute to reduced disc height, altered biomechanics, and pain symptomatology [3, 4]. Traditional nonoperative treatments—including physical therapy, oral medications, and corticosteroid injections—may offer temporary relief but do not address the underlying structural degeneration of the intervertebral disc. Surgical options, such as spinal fusion or total disc replacement, may be inappropriate for patients with moderately severe DDD where preservation of the vertebral motion segment is paramount. Consequently, there exists a significant treatment gap between conservative care measures and invasive surgical procedures in patients with chronic lumbar discogenic pain.

VIA Disc NP is a minimally manipulated, micronized NP allograft processed from donated cadaveric disc tissue and reconstituted in sterile saline at the time of the procedure. Delivered intradiscally under fluoroscopic guidance, it is intended to supplement the degenerated native nucleus with allogeneic matrix material while preserving spinal anatomy. Accumulating clinical evidence shows that this product may result in clinically meaningful improvements in pain, function, and quality of life through 2 years of follow-up following a single treatment [5, 6]. This investigation is designed to evaluate the safety and efficacy of VIA Disc NP in a multi-center, double-blind, sham-controlled randomized clinical trial.

### Objectives {7}

The primary objective is to evaluate the safety and efficacy of a single intradiscal injection of VIA Disc NP in participants with lumbar discogenic pain and magnetic resonance imaging (MRI)-confirmed DDD.

The study aims to determine whether VIA Disc NP supplementation improves pain and functional outcomes compared to sham control, as measured by the proportion of participants achieving a clinically meaningful reduction in back pain severity at 12 months.

Secondary objectives include assessing changes in disability, opioid use, quality of life scores, as well as tracking treatment-emergent adverse events (AE) over 24 months of follow-up.

### Trial design {8}

This is a randomized, double-blind, sham-controlled, multi-center clinical trial with an adaptive design and a planned enrollment of up to 446 participants, including up to 21 participants in an initial non-randomized roll-in phase. Eligible participants are randomized in a 2:1 ratio via permuted block design to receive either VIA Disc NP or sham procedure. Randomization is stratified by site and previous intradiscal biological treatment (Y/N). All participants, clinical personnel, and outcome assessors are blinded to group assignment.

The primary efficacy analysis of this superiority trial will be conducted at 12 months, with long-term efficacy, safety, and exploratory imaging data collected through 24 months. Pre-specified interim analyses will be used to guide the adaptive design while controlling type 1 error inflation and power.

Sham participants who meet crossover criteria at 12 months (visual analog scale (VAS) ≥ 40 mm and ODI ≥ 40) are eligible to receive VIA Disc NP and initiate a secondary 12-month follow-up. All procedures are standardized across sites and performed under moderate conscious sedation using a fluoroscopy-guided technique.

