### Sample size {14}

The sample size for this study is based on a sham success rate assumption of 40% and varying superiority assumptions (delta) from 12.5 to 30 percentage points [17]. For initial study planning purposes, a frequentist *Z*-test for two proportions framework with pooled variance was used to calculate the required sample size to achieve 85% power using a one-sided alpha = 0.025 and 2:1 randomization.

Table 2 shows that when VIA Disc NP performance is 20 percentage points better than sham, *N* = 248 subjects are needed before loss to follow-up (LTFU). When VIA Disc NP performance is 15 percentage points better than sham, *N* = 446 subjects are needed (before LTFU). These sample sizes (*N* = 248 and *N* = 446) are the minimum and maximum number of subjects that will be enrolled (before LTFU).

**Table 2 Tab2:** Range of sample size estimates based on MCID responder rate differences

Sham	Treatment	Delta	*N* (no LTFU)	*N* w/LTFU
40.0%	70.0%	+ 30.0%	107	119
40.0%	60.0%	+ 20.0%	248	276
40.0%	57.5%	+ 17.5%	326	362
40.0%	55.0%	+ 15.0%	446	496
40.0%	52.5%	+ 12.5%	641	712

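### The 446 enrolment cap is Table 2's no-loss figure and includes up to 21 non-randomised roll-ins, so the 85% planning power at a 15-point difference is not carried into the cap

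*Protocol article*

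**What the plan says.** All statements are in the protocol article.

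- **Sample size {14}, method.** The planning test was a "frequentist *Z*-test for two proportions framework with pooled variance". The targets were 85% power, a one-sided alpha of 0.025 and 2:1 allocation. The calculation is "based on a sham success rate assumption of 40" per cent.
- **Sample size {14}, Table 2.** The row for a 15-point difference reads "40.0% 55.0% + 15.0% 446 496". The last two entries are the total without loss to follow-up and the total with it. For a 20-point difference they are 248 and 276.
- **Sample size {14}, range.** The text takes 248 and 446, both from the no-loss column, and says that they "are the minimum and maximum number of subjects that will be enrolled (before LTFU").
- **Trial design {8}.** The cap is a "planned enrollment of up to 446 participants, including up to 21 participants in an initial non-randomized roll-in phase".
- **Sequence generation {16a} and Study setting {9}.** Only participants in the randomisation stage are allocated 2:1, and the roll-in comes before randomisation.
- **Missing data {20c}.** Participants without month-12 data enter the analysis by Bayesian multiple imputation, which may use covariates such as age, sex, body mass index and race/ethnicity.

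**The concern.** A number required for analysis has been used as a limit on enrolment. Two things then come off it. Roll-in participants have no randomised comparator, so they add nothing to the comparison that the power calculation describes. Participants lost before month 12 add little. Table 2 shows that the authors thought loss needed compensation, because it raises 446 to 496, but neither {8} nor {14} adopts 496.

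The 15-point difference is the one that fixes the maximum size. If power there is below the planned 85%, the chance of missing a real benefit of that size is larger than a reader of {14} would believe. Neither type I error nor participant safety is affected.

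**Working it through.** **Inputs.** Sham rate 0.40, active rate 0.55, one-sided alpha 0.025 (z = 1.960), power 85% (z = 1.036), allocation 2:1, pooled variance, all from {14}. Roll-ins up to 21, from {8}. Loss is not stated as a rate. The five rows of Table 2 fit N/0.90: 107, 248, 326, 446 and 641 become 118.9, 275.6, 362.2, 495.6 and 712.2, against the printed 119, 276, 362, 496 and 712. The implied loss is therefore about 10%.

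**Reproducing 446.** Let m be the sham-group size, so N = 3m, and let p̄ = (0.40 + 2 × 0.55)/3 = 0.50.

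- A = √(1.5 × p̄ × (1 − p̄)) = √0.375 = 0.6124
- B = √(0.40 × 0.60 + 0.55 × 0.45/2) = √0.36375 = 0.6031
- N = 3 × (1.960A + 1.036B)²/0.15² = 3 × (1.2002 + 0.6251)²/0.0225 = 444.2

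The printed figure is 446. The other four rows give 106.2, 248.3, 325.7 and 639.8, against 107, 248, 326 and 641. The method is the plan's, to within one or two participants.

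**Power at the numbers the cap allows.** Power = Φ[(0.15 × √(N/3) − 1.2002)/0.6031].

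| Situation at the cap | N contributing | 0.15 × √(N/3) | z | Power at 15 points |
|---|---|---|---|---|
| 446 randomised, no loss (Table 2) | 446 | 1.829 | 1.042 | 85.1% |
| 446 − 21 = 425 randomised, no loss | 425 | 1.785 | 0.970 | 83.4% |
| 446 randomised, 10% loss | 401.4 | 1.735 | 0.887 | 81.2% |
| 425 randomised, 10% loss | 382.5 | 1.694 | 0.818 | 79.3% |

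With 425 randomised, losses of 5%, 15% and 20% give 81.5%, 77.0% and 74.5%. Roll-ins alone cost 85.1 − 83.4 = 1.7 points; loss alone costs 85.1 − 81.2 = 3.9 points and is the larger part.

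**Detectable difference.** Solving the same formula, with A and B recomputed, for 85% power at N = 382.5 gives 16.2 points.

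**Check under the planned decision rule.** An exact calculation with Jeffreys priors and a posterior threshold of 0.975, without interim looks, gives 85.6% at 149 sham and 297 active, and 79.8% at 128 and 255. The shortfall does not come from the choice of planning test.

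**The minimum.** At 40% versus 60% the same method gives 85.0% for 248 and 81.0% for 248 × 0.90 = 223.2.

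**The case against.** The strongest reply is that the 85% is a planning figure from a fixed frequentist design. The trial will use a Bayesian rule with interim analyses, and its operating characteristics may sit in an analysis plan that is not shown. That is right as far as it goes. A reader might infer that the trial's actual power is 79%; the documents do not support this, because the interim rules are not given and 79.3% is itself a fixed-design figure. What stands is that adaptation works within the cap, so it does not remove the conflict between the cap and the table from which it was taken.

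Second, one could read {14} as meaning 446 evaluable, with 496 to be enrolled. But {14} calls 446 the maximum enrolled and {8} repeats it as planned enrolment, with roll-ins inside. If 496 was meant, both sections need correction anyway.

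Third, it would be too strong to say that no allowance for loss was made. Table 2 has a loss-adjusted column; it was not carried into the cap.

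Fourth, imputation may recover some information. The covariate list in {20c} is not closed, and VAS is also measured at months 1, 3 and 6. Counting only participants with month-12 data is therefore an approximation that assumes little recovery.

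Finally, a reader might press the same charge at the minimum and deduct roll-ins there too. {8} ties the roll-ins only to the 446, and 248 is a lower bound in an adaptive design, not the final size whenever the true difference is 20 points. With 382.5 contributing at the cap, fixed-design power at 20 points is about 96%.

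**Conclusion.** The point holds as a mismatch between {8}, {14} and Table 2: the cap does not deliver the 85% planning power at the difference that sets it. Either cause alone takes fixed-design power below 85% (83.4% from roll-ins, 81.2% from loss). Together they give 79.3%, so the type II error at 15 points rises from 15% to about 21%.

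The 79.3% is a worst case within the document's own figures. It needs all 21 roll-in places used, a 10% loss inferred from Table 2, and little information recovered by imputation, and it leaves the interim analyses out. The minimum is a secondary matter: 248 is also a no-loss figure, and a trial that stopped there with 10% loss would have about 81% fixed-design power at 20 points.

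**What to change.** Keep roll-ins inside the 446, as {8} states, and restate {8} and {14} along these lines:

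> Of up to 446 enrolled, up to 21 are roll-ins not included in the randomised comparison, leaving at least 425 randomised at the maximum. Assuming 10% loss to follow-up (about 382 with month-12 data), fixed-design planning power is about 79% for a 15-point difference and 85% for a 16.2-point difference.

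Label 248 and 446 as figures that do not include Table 2's loss allowance. State that 85% power at 15 points corresponds to Table 2's 496 randomised, exclusive of roll-ins (496 + 21 = up to 517 enrolled), so that a sponsor who wishes to keep the 85% claim can see what it rests on.

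The restatement is a wording change in two sections and needs no extra participants. Its only cost is a less favourable stated power.

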## Methods: participants, interventions, and outcomes

### Study setting {9}

The trial is conducted at up to 21 investigational sites across the USA, including academic and private clinical research centers with dedicated interventional spine capabilities. All sites must demonstrate operational readiness and procedural consistency during a roll-in phase prior to randomization. Investigators are board-certified or fellowship-trained in pain management, spine intervention, or a related specialty, and must be proficient in the administration of VIA Disc NP per the manufacturer’s instructions for use (IFU). Each site maintains the capacity for longitudinal follow-up and secure data management in accordance with good clinical practice (GCP) and Institutional Review Board (IRB) standards.

### Eligibility criteria {10}

Eligibility for inclusion is evaluated on a site-specific basis based on each participant’s medical, clinical, and radiographic presentation as well as for study consistency purposes.

To be eligible to participate in this study, participants must meet all of the following criteria:Age 22 to 85 years oldDiagnosis of moderate to severe DDD on MRI, modified Pfirrmann grade 3–7Chronic axial midline low back pain in the absence of lower extremity motor/sensory/reflex changes with or without referred non-radicular leg pain for at least 6 months prior to screening; unresponsive to at least 3 months of conservative careLow back pain severity score of ≥ 40 to ≤ 90 mm on the VASOswestry disability score (ODI) score of ≥ 40 to ≤ 80Positive sustained hip flexion testDemonstrated intolerance to sittingAble to give voluntary, written informed consent to participate and have signed an informed consent form (ICF) specific to this studyWilling and able to comply with all study procedures and availability for the duration of the study with a life expectancy of > 2 years

Clinical notation: During initial physical examination screening, potential study participants will undergo a sustained hip flexion test (inclusion #6). This maneuver is undertaken with the patient in the supine, straight-leg position. Both legs are elevated simultaneously to approximately 45 degrees and then both are allowed to come down slowly. A positive response is determined by patient report of familiar pain and may be corroborated by examiner observation of guarding, facial grimace, or other pain behavior [7].

The sustained hip flexion test is a pragmatic, low-burden clinical maneuver used by investigators in this trial to help distinguish axial discogenic pain from other etiologies. Although not formally validated in large-scale studies, its inclusion reflects real-world practice among experienced interventionalists and may help enrich for patients with centrally mediated axial symptoms rather than peripheral radiculopathy. The protocol operationalizes the test with specific positional and temporal parameters to improve consistency across sites.

Participants who meet any of the following criteria will be excluded from participating in this study:Contraindications to the proposed sedation/anesthetic protocolInvolvement of more than two lumbar discs as evidenced by 3 or more discs with a modified Pfirrmann grade of 3 or greaterDisc height of less than 4 mm for any disc between L1 and S1Symptomatic vertebral compression fracturePrevious surgical treatment of the lumbar spineHistory of sacroiliac (SI) joint fusion within the past 6 monthsReceived lumbar epidural or intradiscal steroid injection, lumbar facet-joint steroid injection, lumbar radiofrequency ablation, provocative or anesthetic discography, SI joint pain injection, injection of methylene blue, dextrose, glucosamine, and chondroitin sulfate, or biacuplasty within 3 months of the day 0 procedure. Received intraosseous radiofrequency nerve ablation procedure at the same or adjacent level (e.g., basivertebral nerve ablation or sinuvertebral nerve ablation)Been a recipient of prior intradiscal stem cell/progenitor cell therapy or other biological intervention (e.g., mesenchymal stromal cells [MSC], platelet-rich plasma [PRP]) at the target intervertebral disc within 12 months of the day 0 procedureEvidence of dynamic instability on lumbar flexion–extension radiographs (> 3 mm)Grade 2 or higher spondylolisthesis at the target level, lumbar spondylitis or other undifferentiated spondyloarthropathy, or type III Modic changes adjacent to the target discRadiographic evidence of a full-thickness annular tear at the target disc or other abnormal disc morphologyClinical suspicion of facet pain as primary pain generatorA systemic condition or disease not stabilized or judged by the investigator to be incompatible with participation in the study (e.g., current systemic infection, uncontrolled autoimmune disease, uncontrolled immunodeficiency disease, recent history of myocardial infarction, uncontrolled diabetes (> 7.0% HbA1C))Received VIA Disc NP previouslyDeemed unsuitable for clinical study participation by the investigatorEvidence of substance abuse (including marijuana); note: participants using prescribed extended-release narcotics (e.g., fentanyl patch, MS Contin, oxycontin) within the 3 months prior to screening and participants on long-acting opioids may be given an option to wean off opiates before enrollment; participants on short-acting opiates (e.g., hydrocodone, oxycodone, tramadol) may be included and utilization monitored after the treatmentOpioid use of more than 90 MME/dayCurrently receiving treatment with radiation, chemotherapy, immunosuppression, or chronic steroid therapy (prednisone, or its equivalent, use of up to 5 mg/qd, or inhalation steroids for asthma is allowed)Metal or ceramic implants in the lumbar spine regionContraindications to MRI, including non-MRI compatible devices and active implantable devices such as spinal cord stimulators and intrathecal pumpsInvolved in ongoing or closed (within 6 months of screening visit) litigation related to their back-pain conditionAny mental instability, unstable bipolar disorders, unmanaged post-traumatic stress disorder (PTSD) or uncontrolled anxiety/depression and/or require new or changed anti-depressants or anti-psychotic medications within 3 months of enrollmentDiagnosis of any traumatic neurological disorders that may impact the study as per the judgment of the investigatorWomen who are pregnant or breastfeeding at the time of enrollment and/or plan to become pregnant during the study; pregnancy is confirmed by:A positive pregnancy test during the screening visitSelf-reported pregnancyWomen of childbearing potential (WOCBP) who are not using a reliable form of contraception (as determined by the investigator)Received any experimental drug or device to treat the same condition used within 6 months prior to the screening visit or during the course of the clinical trialOther persistent pain/nerve issues including radiculopathy, leg pain, and cauda equina syndrome

### Who will take informed consent? {26a}

Patients with MRI-confirmed DDD will be screened for eligibility to participate in this study based on the above-mentioned criteria. After the patient has been assessed as eligible by the treating physician, he/she will receive initial study information. The research team at each clinical site conducts a detailed in-person consultation for eligible patients about all study stages, including information about the objectives, outcome measures, intervention characteristics, risks, benefits, and the confidentiality of data management. Data collection only begins after signing the ICF.

### Additional consent provisions for collection and use of participant data and biological specimens {26b}

This provision is not applicable since this trial does not involve collecting biological specimens for storage. The study’s primary and secondary outcomes use patient-reported outcome measures (PROMs), physical functional tests, and MRI measurements.

## Interventions

### Explanation for the choice of comparators {6b}

Participants randomized to the control arm will receive a sham procedure. The procedure will be identical to the investigational procedure with the following exception: a 20G spinal cannula will be carefully inserted through the skin and muscle of the back but will not penetrate the annulus fibrosus of the intervertebral disc(s). Sham procedures mimic setup, the procedure itself, and sedation but do not involve an intradiscal injection, and no saline or VIA Disc NP will be injected.

### Intervention description {11a}

Participants randomized to the investigational arm will receive VIA Disc NP. A single dose, intradiscal delivery of 100 mg of VIA Disc NP mixed with sterile saline will be administered according to product IFU. All investigators undergo IFU training and demonstrate procedural competency.

### Criteria for discontinuing or modifying allocated interventions {11b}

All treated participants will be followed for the pre-specified duration of the trial and all safety assessments will be completed. No enrolled participants will be exited from the study unless they withdraw consent or based on investigator decision for participant safety. Any participant withdrawn from the study for any reason will have their reason(s) for study discontinuation recorded. Participants may withdraw from the study after signing informed consent for any reason without penalty.

